### Intervention description {11a}

The DCM concept is based on a collaborative model of care that was previously implemented and evaluated within the DelPHi-MV trial [39]. The InDePendent intervention is extended by advanced nursing roles. Therefore, the intervention will be provided by dementia-specifically-qualified nurses, who will take on particular tasks, that are usually performed by primary care physicians. The DCM qualification was based on curricular guidelines of the Federal Joint Committee on the definition of medical tasks that can be transferred to nurses (§63 Para. 3c of the Social Law Book XI in Germany). The developed curricula were evaluated and approved by the Ministry of Health and the Ministry of Families and were used for the first time to enhance nurses’ competencies to overtake tasks of GP in dementia care. A close cooperation between the GP and the DCM is an important part of the intervention. The intervention is multidimensional and will be individually tailored to the patients’ and caregivers’ specific healthcare needs and their social contexts and resources.

In detail, the intervention consists of four main parts: (1) assessment of patients and caregivers’ unmet medical, pharmaceutical, psychosocial, social, and nursing care needs; (2) development of a plan for needs-based activities; (3) implementation of the intervention tasks needed to address unmet needs; and (4) monitoring of the intervention. The intervention is based on the three principles: (i) management of treatment and care, (ii) medication management, and (iii) caregiver support.

The intervention will be facilitated by a developed computerized intervention management system (IMS) to support the nurses in identifying patients’ and caregivers’ unmet needs and in the development and monitoring of the intervention care plan. The rule-based expert decision support system uses predefined algorithms based on special items within questionnaires and automatically identifies unmet needs and subsequently suggests the corresponding specific treatment and care options to address the identified unmet needs. Therefore, individual patient characteristics were matched to a computerized knowledge base. The IMS system was previously used within the dementia care management of the DelpHi-MV trial, providing evidence that IMS improves the systematic identification of unmet needs and the subsequent recommendation of interventions to address these needs [40].

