### Strategies to improve adherence to interventions {11c}

The specialized nurses take care of the PwDs and their individual needs and will handle all interventions and monitor the completion or incompletion of all tasks frequently. To improve the adherence, the specialized nurses are continuously in and close contact with the PwD during the intervention.

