### Outcomes {12}

The primary outcome of the study is the number of unmet needs in the intervention group compared to the waiting-control group 6 months after baseline. Unmet needs will be assessed with the German version of the Camberwell Assessment of Need for the Elderly (CANE). CANE is available in two versions: one for the PwD (if there is no participating caregiver) and one for the informal caregiver (if the caregiver participates in the study). The result of the CANE is a sum of open and unmet needs.

Secondary outcomes include:
Quality of life

The Quality of Life in Alzheimer’s Disease (Qol-AD) will be used to assess participants’ and caregivers’ quality of life [41]. The German version of the Qol-AD is a well-validated instrument for assessing HRQoL in patients suffering from different dementia diseases, especially for those being mild to moderately cognitively impaired [42].
2.Caregiver burden

Caregiver burden will be assessed by using the Zarit Burden Inventory [43].
3.Acceptance of the care model (process evaluation—only in the intervention group)

In addition to the quantitative analyses, we will perform semi-structured, qualitative interviews evaluated by application of qualitative content analysis [44].
4.Overall health status and economic analyses

For the health economic evaluation, health-related quality of life measured by the EQ-5D-5L and the utilization of healthcare services and informal care measured by the Resource Utilization in Dementia Questionnaire (RUD) [45] and the Questionnaire for Health-Related Resource Use in an Elderly (FIMA) [46] will be assessed.

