## Data collection and management

### Plans for assessment and collection of outcomes {18a}

After study inclusion, all participants will receive a baseline assessment in their homes carried out by study nurses in the waiting-control group and dementia specialized nurses in the intervention group. Follow-up assessments will be carried out 6 months after the baseline assessment by the dementia specialized nurses in both study groups.

The primary outcome participants’ unmet needs will be assessed by using the Camberwell Assessment of Need for the Elderly (CANE). It consists of 27 categories (including two categories for the caregiver), which assess participants’ needs in various domains (e.g., living situation, household, nutrition, personal hygiene) followed by a question, whether the participant has an unmet need in this area (yes, no) [49]. CANE has been determined suitable for scientific use in dementia and demonstrates appropriate criterion validity [50]. It can easily be used by a wide range of professionals without formal training.

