### Data management {19}

Study nurses (waiting-control group) and dementia specialized nurses (intervention group) will collect data by usage of a touch-screen tablet during face-to-face interviews with study participants. Data will be documented in electronic case report forms (eCRFs), including automatic plausibility and completeness checks. All data stored locally on the tablet will be encrypted. The Java-based documentation system is based on the concept of offline clients. Each user (i.e., study nurses and DCMs) has an individual login. The client-server stores all data in the project data management system [52]. Secure data transfer from the tablets to the central database will be ensured by the application of virtual private network technology (VPN).

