### Confidentiality {27}

Personal data will be stored separately from participants’ health data. Data storage is managed according to current standards for data security and data privacy, which is documented in the data protection policy by the Institute for Community Medicine. Only the study nurses and DCMs have access to personal data during baseline and follow-up examinations. Paper documents (i.e., IC) will be stored in a secured way. Only authorized persons can access these documents.

Access to the study software based on individual user passwords and a detailed right and role system in which data minimization and security are priorities. The study nurses and DCMs will only be able to review participants and GPs in their personally assigned study region.

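### Assessor type follows study arm at baseline, the sections disagree on who collects the 6-month CANE from controls, and the care-delivering role collects the intervention arm's primary outcome

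*Protocol article*

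**What the plan says.** All references are to the Protocol article.

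- **Primary outcome.** The section Outcomes {12} defines it as follows: "The primary outcome of the study is the number of unmet needs in the intervention group compared to the waiting-control group 6 months after baseline". It is the CANE count, answered by the patient or, if one takes part, by the informal caregiver.
- **Baseline assessor (Plans for assessment and collection of outcomes {18a}).** The home assessment is "carried out by study nurses in the waiting-control group and dementia specialized nurses in the intervention group".
- **6-month assessor (same section).** "Follow-up assessments will be carried out 6 months after the baseline assessment by the dementia specialized nurses in both study groups".
- **Data collection (Data management {19}).** "Study nurses (waiting-control group) and dementia specialized nurses (intervention group) will collect data by usage of a touch-screen tablet", in face-to-face interviews. No time point is given.
- **Roles in the field (Confidentiality {27}).** "Only the study nurses and DCMs have access to personal data during baseline and follow-up examinations".
- **Delivery of care (Intervention description {11a}).** "the intervention will be provided by dementia-specifically-qualified nurses, who will take on particular tasks". The section on adherence {11c} adds that these nurses "will handle all interventions and monitor the completion or incompletion of all tasks frequently".
- **Blinding {17a}.** The study is unblinded, and no independent outcome assessor is mentioned.
- **Use of baseline data (Statistical methods {20a}).** The arms are compared at baseline, and a significant difference leads to adjustment for relevant variables.

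**The concern.** Three features of the measurement combine.

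First, a practice is allocated when its first patient consents (Implementation {16c}), and the arm then decides which type of nurse takes the baseline CANE. A baseline difference in unmet needs may reflect chance, selective recruitment or the assessor, and the data cannot tell these apart.

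Second, the control arm's assessor at the primary time point is not settled. Under {18a}, the assessor type matches across arms at 6 months but changes between baseline and follow-up in controls only. Under {19}, read literally, it differs by arm at 6 months as well.

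Third, the intervention exists to close unmet needs, and the role that closes them also collects the count of those still open. In controls, under {18a}, the same role collects the count as those patients are about to enter its care. A tendency to see needs as closed after one's own care, or as open before it, would favour the intervention.

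At stake is whether the 6-month difference reflects patients or assessors. An assessor effect aligned with arm cannot be cleanly removed in the analysis.

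**Working it through.** **Who assesses, by reading**

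| | Control | Intervention |
|---|---|---|
| Baseline ({18a}) | study nurse | specialized nurse |
| 6 months, per {18a} | specialized nurse | specialized nurse |
| 6 months, per {19} read without a time limit | study nurse | specialized nurse |

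The intervention column never changes: the care-delivering role collects the outcome on either reading. Only the control cell at 6 months is in doubt. {27} does not settle it, because it names both roles at both examinations without tying them to arms.

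**Direction if the two nurse types differ in how many needs they record**

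Let g be the extra needs that a specialized nurse records on the same patient, and b the slope of the 6-month count on the baseline count. Neither is in the protocol. As assumptions, take g = 0.3 to 0.6 and b = 0.5.

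- {18a} reading, unadjusted: assessor type is equal at 6 months, so g contributes nothing.
- {18a} reading, adjusted for baseline CANE: the baseline of the intervention arm is inflated by g, which shifts the estimate by b × g = 0.5 × 0.3 to 0.5 × 0.6 = 0.15 to 0.30 needs **toward** the intervention.
- {19} reading, unadjusted: g is added to the intervention arm, so 0.3 to 0.6 needs **against** the intervention.
- {19} reading, adjusted: g − b × g = 0.15 to 0.30 needs **against** it.

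If specialized nurses record fewer needs, every sign reverses.

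**How often the baseline route would open**

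Adjustment depends on a significant baseline difference. Inputs from Sample size {14}: SD 2.0, 155 and 310 patients, ICC 0.16, five patients per practice.

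- Design effect = 1 + (5 − 1) × 0.16 = 1.64.
- SE = 2.0 × √(1/155 + 1/310) × √1.64 ≈ 0.25.
- g = 0.3: z ≈ 1.2, significant about 22% of the time.
- g = 0.6: z ≈ 2.4, significant about 66% of the time.

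**Scale of a net bias at 6 months**

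The plan's effect reproduces: 1.87 × 0.65 = 1.2155, rounded to 1.22; 1.87 − 1.22 = 0.65. The 345 analysable patients split 1:2 into 115 and 230.

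- SE = 2.0 × √(1/115 + 1/230) × √1.64 = 0.293.
- With no true effect and a bias B favouring the intervention, the two-sided 5% test rejects with probability Φ(B/SE − 1.96) + Φ(−B/SE − 1.96).

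| B (needs) | Share of 0.65 | Two-sided error |
|---|---|---|
| 0 | 0% | 5.0% |
| 0.1 | 15% | 6.3% |
| 0.2 | 31% | 10.5% |
| 0.3 | 46% | 17.6% |
| 0.4 | 62% | 27.7% |

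This is a normal approximation for a difference in means, not the planned multi-level Poisson model. B is an assumption throughout.

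**The case against.** The strongest defence is that {18a} is the governing section on outcome assessment and is explicit about 6 months. {19} is about tablets and electronic forms, and may simply describe baseline. Controls move to the intervention after 6 months, so a specialized nurse seeing them then can be squared with its wording. This has force: it is an ambiguity within one document that a short phrase would cure. But {19} states no limit, and the point left open is who collects the primary outcome from controls.

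A second defence is that the patient or caregiver answers a yes/no question per category, so the nurse has limited discretion. That makes a large assessor effect less certain. It does not remove the influence of being interviewed by someone from the role that has provided, or is about to provide, the care.

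A third is that blinding is impossible. That holds for those giving care, but it does not explain why they must also assess. {18a} itself describes CANE as usable by many kinds of professional without formal training. The independent evaluation in {5d} and {21a} concerns the results, not the collection of CANE.

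Three stronger readings are tempting and are not supported:

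- *Each nurse scores her own patients.* The text identifies a role. Restricting nurses to their assigned region {27} makes it likely that the same individual assesses, but not certain.
- *Any difference between nurse types inflates the benefit.* If specialized nurses record more needs, the {19} reading works against the intervention.
- *Baseline adjustment will carry the assessor gap into the result.* The primary outcome is the 6-month count, adjustment is conditional, and {20a} does not name baseline CANE as a covariate.

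**Conclusion.** The concern holds in three parts. Baseline assessor type is tied to arm, so the baseline comparison of unmet needs is not interpretable as a check on randomization. {18a} and {19} must be reconciled on the 6-month assessor, because the literal reading of {19} confounds assessor type with arm at the primary time point. On either reading, the care-delivering role collects the unblinded primary outcome in the intervention arm.

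The documents do not show how large the bias is or that it favours the intervention overall. A difference in detection between nurse types can push either way, depending on its sign, the section followed and whether baseline is adjusted for. A tendency to see needs as closed after one's own care favours the intervention, and its size is unknown. The 10.5% error at a bias of 0.2 needs is a scale, not an estimate. It rests on the plan's SD, ICC and cluster size, and on 345 analysable patients. A reader might conclude that assessors alone could account for the primary result; nothing in the protocol establishes that.

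**What to change.** 1. State one rule in both {18a} and {19}: the same staff category collects the 6-month CANE in both arms, and no specialized nurse assesses a patient from her own current or upcoming caseload. Existing specialized nurses can swap 6-month interviews. The telephone or video route mentioned in the Discussion can be used where needed, under the same mode rule in both arms.
2. Record assessor ID and type at every visit.
3. Do not treat a baseline CANE difference as evidence of failed randomization or let its significance decide the model. Report the primary effect with and without baseline CANE adjustment.
4. Add a sensitivity analysis for patients assessed before the change.

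The cost is a protocol amendment, some scheduling or travel time, and a change to the region-restricted software access in {27}. Enrolment began in January 2021, so there will be two assessment regimes, before and after the amendment. The swap does not blind the assessor; it only removes the interest in one's own caseload. A separate study-nurse baseline visit in the intervention arm is not proposed: it would add an assessment for up to 155 patients, and the protocol gives no staffing figures to show that this is feasible.

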### Plans to promote participant retention and complete follow-up {18b}

The DCM will be in frequent contact with both the GPs and the PwD and their relatives. They can address any upcoming questions and concerns. We will provide internal trainings, newsletters, information events, and regular project meetings to maintain the awareness and motivation of all study partners. All changes including revocation of consent or discontinuation of participation will be documented in the study software.

### Data management {19}

Study nurses (waiting-control group) and dementia specialized nurses (intervention group) will collect data by usage of a touch-screen tablet during face-to-face interviews with study participants. Data will be documented in electronic case report forms (eCRFs), including automatic plausibility and completeness checks. All data stored locally on the tablet will be encrypted. The Java-based documentation system is based on the concept of offline clients. Each user (i.e., study nurses and DCMs) has an individual login. The client-server stores all data in the project data management system [52]. Secure data transfer from the tablets to the central database will be ensured by the application of virtual private network technology (VPN).

### Confidentiality {27}

Personal data will be stored separately from participants’ health data. Data storage is managed according to current standards for data security and data privacy, which is documented in the data protection policy by the Institute for Community Medicine. Only the study nurses and DCMs have access to personal data during baseline and follow-up examinations. Paper documents (i.e., IC) will be stored in a secured way. Only authorized persons can access these documents.

Access to the study software based on individual user passwords and a detailed right and role system in which data minimization and security are priorities. The study nurses and DCMs will only be able to review participants and GPs in their personally assigned study region.

### Plans for collection, laboratory evaluation, and storage of biological specimens for genetic or molecular analysis in this trial/future use {33}

Not applicable.

## Statistical methods

### Statistical methods for primary and secondary outcomes {20a}

All statistical analyses will be conducted using pseudonymized data. Initially, primary and secondary outcomes will be analyzed with descriptive analyses. At baseline, the randomization procedure will be verified by comparison of the intervention- and waiting-control group based on descriptive statistics for various variables (randomization check). Should significant differences between the intervention and waiting-control group be identified, analyses will be adjusted for relevant variables. Quantitative parameters will be evaluated using hierarchical multi-level analyses to consider the study design with cluster randomization using physician’s practice and physician’s networks as context variables.

Response rates will be calculated for each group at each time point of analysis and compared between groups. Due to the expression (data count variable) of the primary outcome (unmet needs), a (multi-level) Poisson regression model based on the intention-to-treat principle will be fitted.

Respective to the secondary outcomes, analyses will apply linear or logistic regressions. Concerning the within-trial cost-effectiveness analysis, the incremental cost-effectiveness ratio (ICER) will be calculated by application of the incremental cost per QALY (Quality-adjusted life years) gained by the intervention compared with the waiting-control group. Descriptive statistics will be used to demonstrate unadjusted incremental cost and QALY. Nonparametric bootstrap resampling will be used to handle sampling uncertainty in the ICER. The probability of cost-effectiveness will be calculated by the application of different willingness-to-pay (WTP) margins based on the net monetary benefit approach [53]. All analyses will be performed with the statistical software IBM SPSS Statistics (version 26.0.0.0. or later, IBM Corp., NY, USA) and STATA (version 16 or later, StataCorp. LLC, TX, USA).

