### Sample size {14}

The primary endpoint of this study is the number of unmet needs. Recent literature points out that PwDs have on average 1.87 unmet needs with a standard deviation of 2.0 [47]. The sample size calculation was based on an assumed reduction of the number of unmet needs of 35% and a randomization ratio of 1:2 (1: intervention group, 2: waiting list). In a previous study, where dementia care management was also carried out, and patients were recruited from GP practices, there was an intra-cluster correlation (ICC) of 0.16 with a variance of ICC of 0.06 and a cluster size of five (five patients per GP practice). This ICC, variance of ICC, and cluster size were also used to calculate the sample size for this study. Therefore, a sample size of *n* = 345 PwD and 69 clusters would be needed to demonstrate an implicit effect of 1.22 unmet needs in the intervention group compared to 1.87 unmet needs in the control group at a significance level of *α* = 0.05 and statistical power of 80%. A loss to follow-up of about 30% was assumed due to the elderly population and the inclusion of a waiting-list group. Overall, this requires the recruitment of *n*=465 participants of 93 clusters to demonstrate a significant intervention effect. Therefore, a total of *n* = 310 patients in the waiting-control group (recruited from 62 GP practices) and *n* = 155 patients in the intervention group (from 31 GP practices) will be necessary to detect a significant difference between the intervention and the waiting control group concerning a 35% reduction of unmet care needs.

The randomization ratio of 1:2 was used due to the higher probability of dropouts in the waiting control group, which is predominantly a problem in times of the COVID-19 pandemic and the introduced lockdowns, contact restriction and the high risk of severe COVID-19 progressions, subsequent hospitalization, and death in the elderly population.

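### Significant baseline differences decide whether the analyses are adjusted; the covariates, with baseline unmet needs among them, should be fixed in advance

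*Protocol article*

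**What the plan says.** All of the relevant text is in the protocol article, mostly under Statistical methods for primary and secondary outcomes {20a}.

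- **Baseline comparison.** The arms are compared "based on descriptive statistics for various variables (randomization check"). The variables are not listed.
- **Trigger.** The next sentence reads "Should significant differences between the intervention and waiting-control group be identified, analyses will be adjusted for relevant variables". No test, significance level or list of relevant variables is given.
- **Primary model.** For the count of unmet needs, "a (multi-level) Poisson regression model based on the intention-to-treat principle will be fitted". Multilevel analyses are planned "using physician’s practice and physician’s networks as context variables", and these two terms do not depend on the baseline comparison.
- **Outcome and baseline data.** Outcomes {12} says "The primary outcome of the study is the number of unmet needs in the intervention group" is compared with the waiting-control group 6 months after baseline, measured by the CANE. Section {18a} says "all participants will receive a baseline assessment in their homes carried out by study nurses in the waiting-control group and dementia specialized nurses"; the latter rate the other arm. At 6 months, dementia specialized nurses assess both arms. A baseline CANE for every participant is clearly implied, though not stated outright.

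**The concern.** A baseline difference that reaches significance shows that the arms happen to differ on that variable. It does not show that the variable predicts the outcome. A rule built on it can admit a weak predictor that is imbalanced by chance and leave out a strong one that is not. Baseline unmet needs is the natural predictor of unmet needs at 6 months, yet under the stated rule nothing guarantees its place in the model.

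Two things are at stake. The first is precision: adjusting for a prognostic baseline value shrinks the residual variance whether or not the arms are balanced on it. The second is that the primary model is not fixed until the baseline data have been inspected, and which variables then count as relevant is left open.

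The design adds a further difficulty. Baseline is rated by different nurse types in the two arms, and under Implementation {16c} a practice is allocated when its first patient consents, so later patients can enter after allocation. A significant baseline difference may then reflect the rater or the recruitment, and the rule cannot tell these from chance.

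**Working it through.** **Inputs from Sample size {14}.** "PwDs have on average 1.87 unmet needs with a standard deviation of 2.0"; target 1.22 against 1.87, a difference of 0.65; allocation 1:2; ICC 0.16; five patients per practice; α = 0.05 (two-sided assumed); power 80%; loss about 30%; 465 recruited (155 + 310). The correlation r between baseline and 6-month unmet needs is **not given**, so a range is shown.

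**The plan's own figure.** Without clustering, the total is (1.96 + 0.8416)² × 2.0² × (3 + 1.5) / 0.65² = 334.4, so 335 (112 + 223), close to the stated 345. With design effect 1 + 4 × 0.16 = 1.64 it is 335 × 1.64 ≈ 549. The stated 345 is therefore not reproduced when an ICC of 0.16 is applied in the usual way. Likewise 345 / 0.7 = 493, and 465 corresponds to a loss of 1 − 345/465 = 25.8%. These are separate matters. The present point does not rest on them, but they leave less precision to spare.

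**Power with and without adjustment.** At 30% loss, 108.5 + 217 = 325.5 patients remain. The unadjusted SE is 2.0 × √[DE × (1/108.5 + 1/217)]. Adjustment multiplies it by √(1 − r²), and power is Φ(0.65/SE − 1.96).

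- If loss shrinks practices to 3.5 patients: DE = 1 + 2.5 × 0.16 = 1.40, SE = 0.278.
- If practices keep five patients: DE = 1.64, SE = 0.301.

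| r (assumed) | variance factor 1 − r² | power, 3.5 per practice | power, 5 per practice |
|---|---|---|---|
| unadjusted | 1 | 65% | 58% |
| 0.3 | 0.91 | 69% | 62% |
| 0.4 | 0.84 | 72% | 65% |
| 0.5 | 0.75 | 77% | 70% |
| 0.6 | 0.64 | 83% | 77% |

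**What the triggered rule delivers.** A simulation on practice means used 23 against 46 practices of five (345 analysed), ICC 0.16 at baseline and follow-up, the same r at both levels, one baseline variable tested at 5%, and 40,000 runs per setting.

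| r | power, never adjusted | power, always adjusted | power, adjusted only if baseline p < 0.05 | type I error of the triggered rule |
|---|---|---|---|---|
| 0.3 | 59% | 63% | 59% | 4.8% |
| 0.5 | 59% | 71% | 60% | 4.4% |
| 0.6 | 59% | 77% | 60% | 4.1% |
| 0.7 | 59% | 86% | 61% | 3.5% |

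At r = 0.5 the SD of the estimate is 0.292 unadjusted, 0.282 under the trigger and 0.255 if always adjusted. The trigger keeps little of the available gain.

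**How large an imbalance passes unadjusted.** With 345 analysed, SE = 2.0 × √[1.64 × (1/115 + 1/230)] = 0.2925, so significance needs a baseline difference above 1.96 × 0.2925 ≈ 0.57 unmet needs. The target effect is 0.65.

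**Exposure to a rater difference.** The adjusted estimate is the follow-up difference minus slope × baseline difference. With an assumed slope of 0.5 and an assumed rater offset of 0.3 needs, it shifts by 0.5 × 0.3 = 0.15, against a target of 0.65.

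**The case against.** **The text names no test.** It speaks of descriptive statistics and then of significant differences. A significance test is the natural reading but not a stated one. That limits the wording of the point, not its substance: under any reading, observed imbalance decides the adjustment.

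**Listing covariates is work for the analysis plan.** This is fair as far as it goes. A reader might infer that the article excludes baseline CANE or other fixed covariates; it does not say so, and its silence is no finding. What can be criticised is the trigger it does state, which an analysis plan following it would inherit. Nor is physician network missing, since it is in the model unconditionally.

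**Validity is not harmed.** This stands for the case examined. A reader might infer inflated type I error, but the simulated rate stayed below 5%. Free choice among several relevant variables was not simulated.

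**Trigger frequencies are uncertain.** One might say that adjustment fires by chance in 40% of trials (1 − 0.95¹⁰) and that baseline CANE is left out in 95%. The first needs ten independent tests, a number the article does not give. The second needs true randomisation and a correctly sized test. A test that ignores clustering would fire in about 13% of trials: 2 × [1 − Φ(1.96/√1.64)]. Rater or recruitment differences could raise this further.

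**Forced adjustment can do harm here.** This is the strongest objection, and it stands in part. Follow-up uses one nurse type and baseline uses two, so adjusting for baseline brings any rater offset into the estimate. The current rule does not avoid this: an offset makes the trigger more likely to fire, so adjustment happens where the offset is largest. The answer is to report both models, not to keep the trigger.

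**Conclusion.** The point holds as a matter of efficiency and prespecification. The stated rule makes the primary model depend on observed baseline differences and usually forgoes the precision that baseline unmet needs could give.

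The size depends on r. Always adjusting adds about 4 percentage points of power at r = 0.3, about 12 at r = 0.5 and about 18–19 at r = 0.6; the triggered rule adds at most about 1–2 in the simulation. These figures rest on an assumed r, the same r at practice and patient level, a two-sided 5% test, and a normal approximation to a mean difference in place of the planned multilevel Poisson model. It should not be inferred that adjustment restores 80% power. With five patients per practice it is 77% even at r = 0.6, and 80% is passed at that r only if practices shrink to 3.5 patients.

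**What to change.** Replace the trigger sentence with:

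> The primary multilevel Poisson model includes a prespecified covariate set, with baseline CANE unmet needs, regardless of observed balance. Physician network and practice stay as context variables. Secondary outcomes include their own baseline value. The baseline comparison is descriptive and does not determine the model.

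Also prespecify and report the primary model without baseline CANE as a sensitivity analysis, and read any difference between the two as a possible rater offset at baseline.

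The cost is a short change of text and a little more analysis on data the trial already plans to collect. No change of raters is required. The downside is that the adjusted estimate is exposed to any baseline rater difference between the arms, which the sensitivity analysis is there to show.
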